### Primary outcome

Log SCr measured from the blood sample taken at 2, 30 and 90 days (part of the standard of care) after endovascular revascularisation.

### Secondary outcomes

#### Key secondary outcome

Volume of iodinated contrast medium used during endovascular revascularisation.

The trial is adequately powered to assess both the primary outcome and the key secondary outcome. This will provide clinicians with high-quality definitive evidence and data necessary in order to adopt this intervention into their routine clinical practice.

#### Other secondary outcomes

Proportion of participants developing AKI (per stage of AKI) within 2 days (48 hours) of procedure based on the KDIGO definition of AKI-stages.Proportion of participants developing MAKE by 90-day follow-up. A MAKE event is defined as either death, new requirement for dialysis or worsening kidney function, denoted by >25% decline in eGFR. Baseline eGFR will be defined as the most recent value before the procedure.Time spent as an inpatient (days) since randomisation measured using patient medical records by a 90-day follow-up.Pain experienced during the procedure was measured using a Visual Analogue Scale (VAS).Quality of life (QoL) at 90-day follow-up was measured using the EQ-5D-5L (European Quality of life 5 Dimensions 5 Levels questionnaire) and Social Function - 46 items (SF-36) questionnaires.The proportion of revascularisation completed as planned, measured using patient medical records at one time point.Number of surgical or endovascular reinterventions measured using patient medical records by the 90-day follow-up.Perceived acceptability, feasibility and factors that may influence the adoption of CO_2_ during each revascularisation by the practitioners/participants were measured using the Theoretical Framework of Acceptability (TFA) Questionnaire at the 90-day follow-up for patients, and postprocedure (administered within 3 days of the intervention) and cross-sectional questionnaires (administered after a few months into recruitment) for practitioners.Costs associated with each procedure (health economic analysis) measured using a Healthcare Resource Use questionnaire over a minimum 90-day period (end of clinical follow-up).

Fluid therapy and medical care per patient will be documented for both groups before and after the procedures, using a standardised data collection system, based on our completed NIHR-Research for Patient Benefit funded Community and Hospital cAre Bundle to improve the medical treatment of severe cLaudIcation and critical limb iSchaemia (CHABLIS) study.^13 14^ Further, all equipment/devices used in each procedure will also be collected, and the duration of the procedure will be documented, to allow an in-depth health-economic analysis (additional package funded separately).

### Participant timeline and schedule of events

Participants will be screened and consented up to 15 days prior to the index procedure. Baseline assessments include medical history, demographics, height, weight, baseline SCr and patient-reported outcome measures relating to QoL (using the patient-preferred EQ-5D-5L and SF-36 forms).

Randomisation occurs after consent and baseline measurements, allocating participants 1:1 to iodinated contrast medium or CO_2_ via an automated injector. The index procedure (endovascular revascularisation) will be performed within 15 days of consent.

Follow-up assessments will coincide with routine NHS care at Days 2, 30 and 90 after the procedure. These include SCr measurements, repeat patient-reported outcome measures (Day 90), pain scores (VAS during the index procedure) and healthcare resource use questionnaires (Day 90).

An optional qualitative interview will be offered 3–4 weeks postprocedure to a purposive sample of participants and practitioners to explore intervention acceptability and implementation factors.

### Statistical considerations

#### Sample size calculation

174 patients (87 per group) provide 90% power to detect clinically meaningful differences. Based on our preliminary data (observational AKI study of 2021 patients with PAD/CKD treated in three sites and a pilot study on the use of CO_2_ in PAD procedures),^78 15^,^17^ we expect the SD of log SCr values at 2, 30 and 90 days to be 0.25 log (µmol/L). We assume the correlation of the baseline, 2, 30 and 90-day measures to be 0.67, which is conservative. With these assumptions, a sample size of 156 patients (78 per group) would have a 90% power to detect a mean difference of 0.075 log (µmol/L) in SCr values (effect size of 0.3) at 2, 30 and 90 days postsurgery, between intervention and control groups with an alpha value of 0.05. Allowing for a 10% drop-out, 174 will be recruited. This sample size will also allow us to assess for a 20% reduction in the volume of iodinated contrast used in those having the intervention versus control (median of 70 mL of iodinated contrast used in our published series without CO_2_). In order to ensure the population remained truly per intention-to-treat (ITT) for the primary outcome, multiple imputation will be implemented to deal with missing data in instances where participants are missing any of the SCr values. Values will be predicted using a multivariate normal regression equation with 20 imputations being used.

#### Recruitment

Potential participants will be identified during routine clinical care in NHS vascular clinics and multidisciplinary team meetings at participating sites. Patients scheduled for endovascular revascularisation who meet the inclusion criteria will be approached by local clinical teams. Eligible patients will be provided with verbal and written information about the trial and given sufficient time to consider participation.

Written informed consent will be obtained by trained research staff prior to any trial-specific procedures. Recruitment will be supported by site investigators, research nurses and the wider clinical team. Patient and public involvement and engagement (PPI and E) representatives have reviewed all participant-facing materials to ensure clarity and acceptability. Recruitment will be monitored by the coordinating team, with regular feedback provided to sites to maintain recruitment targets across all participating NHS trusts.

Participating NHS organisations/trusts (recruiting sites):

University Hospitals of Leicester NHS Trust.

Manchester University NHS Foundation Trust St George’s NHS Trust.

Hull University Teaching Hospitals NHS Trust.

University Hospitals of North Midlands.

St George’s University Hospitals NHS Foundation Trust.

Royal Free London NHS Foundation Trust.

#### Assignment of interventions and randomisation

1:1 electronic randomisation. Minimisation based on CKD stage, age, diabetes and tissue loss.

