### Trial setting

Six NHS hospital sites in England providing arterial intervention services, which are already using the Angiodroid CO_₂_ injector. Preoperative and postoperative care will follow local protocols of care (pragmatic RCT).

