#### Data analysis

The LCTU Trial Statistician will be responsible for planning, monitoring and carrying out analyses, supervised by a senior statistician. Statistical analysis will be undertaken according to a prespecified statistical analysis plan (SAP) written prior to database lock and reported following Consolidated Standards of Reporting Trials statements. The baseline characteristics of the participants will be summarised by group. Continuous variables will be summarised using mean and SD, or median and IQR if data do not have a symmetric distribution. Categorical variables will be summarised with counts and percentages. The primary analysis of the primary outcome will be carried out in the ITT population using a mixed effects model with participant as a random effect to account for repeated measures over time. Each participant will contribute up to three repeated outcome measures to the model in addition to the baseline SCr. The model will be adjusted for the stratification and minimisation variables (age, sex, baseline CKD stage and presence of tissue loss). Secondary outcomes will be analysed on a complete case population and reported similarly to the primary outcome using appropriate methodology to compare randomised groups; binary outcomes using logistic regression, continuous outcomes using linear regression or, where not normally distributed, using appropriate non-parametric methods.

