### Statistical methods

#### Planned analyses for primary and secondary outcomes

The primary analysis will be performed on an ITT basis, including all randomised participants as allocated. The primary outcome—log SCr at 2, 30 and 90 days postprocedure—will be analysed using a mixed-effects model with participant as a random effect to account for repeated measures over time. The model will adjust for baseline log SCr, stratification and minimisation factors (age, sex, baseline CKD stage and presence of tissue loss).

Secondary outcomes will be analysed using appropriate statistical methods: binary outcomes (eg, AKI incidence, MAKE) will be compared between groups using logistic regression; continuous outcomes (eg, contrast volume, QoL scores) will be analysed using linear regression, or non-parametric tests if data are not normally distributed. Time-to-event data, if applicable, will be analysed using survival analysis methods such as Kaplan-Meier estimates and Cox proportional hazards regression. All analyses will be conducted using validated statistical software according to a prespecified SAP.

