## Discussion

The KID trial addresses a critical and currently unmet need in the management of patients with PAD and CKD undergoing endovascular intervention (1). AKI is a common and serious complication in this population, largely attributed to the use of iodinated contrast medium. This multicentre, RCT will evaluate whether the use of CO_₂_ delivered via an automated injector (Angiodroid) can reduce the incidence and severity of renal impairment in the short and medium term, compared with standard iodinated contrast.

While previous observational studies have indicated a potential benefit of CO_₂_ angiography in preserving renal function, this will be the first trial to evaluate its use systematically in a PAD/CKD cohort using robust clinical, implementation and health economic endpoints. Incorporating a mixed-methods process evaluation and qualitative analysis ensures that acceptability, feasibility and implementation barriers are explored in both patients and practitioners.

Several practical and operational challenges are anticipated. These include variation in operator experience with CO_₂_ delivery, ensuring high-quality imaging and managing procedural discomfort, which some patients may experience. Further, CO_₂_ injectors are not yet widely used across all NHS centres, requiring site-specific support and training. Patient follow-up at three separate time points (2, 30 and 90 days) also presents logistical demands, particularly in a population that may have mobility or access issues.

Nonetheless, the trial is strengthened by its pragmatic design, national recruitment strategy and the use of existing NIHR infrastructure. A data management plan and engagement with experienced vascular centres will help ensure consistency in intervention delivery and data collection. The trial has been codeveloped with extensive PPI&E, ensuring relevance of outcomes and acceptability of follow-up protocols.

If successful, the KID trial could support a shift in clinical practice by providing definitive evidence on the utility of automated CO_₂_ angiography in reducing AKI, potentially influencing NICE guidelines and NHS resource allocation. A reduction in AKI incidence could not only improve clinical outcomes but also yield substantial cost savings for the healthcare system. The findings will therefore have significant implications for both clinical and policy decision-making in vascular care.

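### Care follows local protocols at six hospitals, but hospital is neither a minimisation factor nor a listed term in the primary model, which costs precision though not validity

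*Protocol article*

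**What the plan says.** The trial runs at "Six NHS hospital sites in England providing arterial intervention services" (Protocol article, Trial setting). The same section states: "Preoperative and postoperative care will follow local protocols of care (pragmatic RCT". Under Interventions, operators in the CO2 arm may add iodinated contrast when they judge it necessary.

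The allocation rule is "1:1 electronic randomisation. Minimisation based on CKD stage, age, diabetes and tissue loss" (Assignment of interventions and randomisation).

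The primary model is described twice:

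- Data analysis: "The model will be adjusted for the stratification and minimisation variables (age, sex, baseline CKD stage and presence of tissue loss".
- Planned analyses for primary and secondary outcomes: "The model will adjust for baseline log SCr, stratification and minimisation factors (age, sex, baseline CKD stage and presence of tissue loss". Here the model is a "mixed-effects model with participant as a random effect to account for repeated measures over time".

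Hospital appears in neither covariate list, and no hospital-level random effect is named. Both lists mention stratification, but the article identifies no stratification variable.

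Iodinated contrast volume, the key secondary outcome, is to be analysed by linear regression, or by a non-parametric method if it is not normally distributed. No hospital term is named for it.

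**The concern.** Local practice in fluids, medication around the procedure and postoperative care can change creatinine after the procedure. In a pragmatic trial, hospital is the natural marker of such practice. Allocation is not balanced within hospital, so by chance one arm can hold more patients from hospitals whose patients fare better after the procedure. The listed model has no term that takes this out.

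Adjustment for baseline log creatinine and CKD stage deals with hospitals whose patients simply start with worse kidneys. It does not deal with hospitals that differ in how creatinine moves afterwards. Contrast volume is more exposed, because it has no baseline value to adjust for. Differences between hospitals in how much iodinated contrast is customary go straight into its error term.

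At stake is the width of the confidence interval and the power for these two outcomes.

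**Working it through.** **Inputs from the article (Sample size calculation).** SD of log creatinine 0.25; correlation 0.67 among baseline and the three follow-up measures; target difference 0.075; alpha 0.05 (taken as two-sided); power 90%; 78 per group; 10% drop-out. The number of hospitals is six.

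**Reproducing the plan's figure.** For the mean of three follow-up values adjusted for baseline, the variance factor is (1 + 2×0.67)/3 − 0.67² = 0.7800 − 0.4489 = 0.3311. The residual variance is 0.25² × 0.3311 = 0.02069, so the SD is 0.144. With 78 per group the SE is √(2 × 0.02069/78) = 0.0230. This needs 78 per group, power is 0.9025, and 156/0.9 gives 174 after rounding up. The plan's figures reproduce.

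**Not in the article.** The share of the baseline-adjusted variance that lies between hospitals is not given. It is assumed here to range from 0 to 20%.

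**Chance difference between arms due to hospital.** Take six equal hospitals of 26 and an overall 78:78 split that is not balanced within hospital. If the between-hospital SD is s, the variance of the hospital-driven difference is about s² × (5/6) × (156/155) × (2/78) = 0.0215 s², so its SD is 0.147 s. At a 10% share, s = √(0.10 × 0.02069) = 0.0455, giving 0.147 × 0.0455 = 0.0067.

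A simulation agrees with this. It used 4,000 runs per setting, with six hospitals either equal or sized 60, 36, 24, 16, 12 and 8:

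| Hospital share | s | SD of chance difference | 95th percentile (absolute) | Percent of 0.075 |
|---|---|---|---|---|
| 2% | 0.020 | 0.003 | 0.006 | 8% |
| 5% | 0.032 | 0.005 | 0.009–0.010 | 13% |
| 10% | 0.045 | 0.006–0.007 | 0.013 | 17–18% |
| 20% | 0.064 | 0.009 | 0.018–0.019 | 24–26% |

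The median, over runs, of the largest difference in arm counts within any one hospital was 6–8 patients.

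**Power with 156 analysed.** Hospital variance may already be contained in the planned variance, or it may come on top of it:

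| Hospital share | Contained: without / with hospital terms | On top: without / with hospital terms |
|---|---|---|
| 0–5% | 0.90–0.91 / 0.89–0.91 | 0.89–0.90 / 0.88–0.89 |
| 10% | 0.90–0.91 / 0.92 | 0.87 / 0.88–0.90 |
| 20% | 0.90–0.92 / 0.95 | 0.83–0.84 / 0.90 |

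The simulation error of each power value is about √(0.9 × 0.1/4000) = 0.005, so differences of 0.01 carry little weight.

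Check of the last cell without hospital terms: a 20% share on top means s² = 0.02069/4 = 0.00517. The variance of the estimate is 0.0215 × 0.00517 + (2/78) × 0.02069 = 0.000642, so the SE is 0.0253. Power is then Φ(0.075/0.0253 − 1.96) ≈ Φ(1.00) = 0.84.

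**Validity.** Without hospital terms, the mean estimate was 0.075 throughout, and type I error was 0.046–0.053.

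**Contrast volume.** The article gives a median of 70 mL and a target reduction of 20%, but no SD, so the loss for this outcome cannot be computed.

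**The case against.** The strongest reply is that the article may not show the whole model. It speaks of stratification variables without naming any. Its bracketed list does not match its own minimisation factors: diabetes is minimised but not listed, and sex is listed but not minimised. Hospital could be a stratifier in the full protocol or a term in the SAP. This stands as a reason for caution, but it does not dispose of the point. The covariates are spelled out twice without hospital. If hospital is a stratifier, the listed model omits a design factor.

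The second reply is that the loss may be close to nothing. This also stands. No between-hospital variance is given, and the SD of 0.25 draws partly on data from three sites, so it probably already contains some hospital variation. At shares up to 5%, hospital terms gain nothing and may cost about one percentage point of power.

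A reader might infer that the treatment effect would be biased, or that hospital differences are never removed. The documents support neither. Allocation is randomised, so any imbalance is chance, and the test and interval already allow for it. Baseline creatinine and CKD stage take out stable differences.

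A reader might also point to the Discussion, which expects "variation in operator experience with" CO2 delivery. That is tied to operators rather than hospitals, and the sites are ones "which are already using the Angiodroid" injector. Skill with CO2 acts mainly in the CO2 arm, so it is variation in the treatment effect. A hospital main effect would not remove it.

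**Conclusion.** The point holds as one of precision. As the article states the plan, hospital is absent from both the allocation rule and the primary model, although care is local at six hospitals. What stays in the error term is hospital variation in creatinine change after the procedure and in contrast volume.

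For the primary outcome, the loss ranges from negligible (assumed share 0–5%) to a fall in power to 0.83–0.84 (share 20%, on top of the planned variance). In that worst case, hospital terms bring power back to about 0.90. The lower part of the range is at least as plausible as the upper, and nothing in the article settles it. The figures assume hospital effects common to both arms, 156 participants analysed, and allocation unrelated to hospital; the four-factor minimisation was not itself simulated.

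The absence of hospital from the stated lists is certain. The size of the effect is not. The stated sample size of 156, or 174 with drop-out, does not change.

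**What to change.** Add hospital to the primary model in both places where it is described, as a fixed effect or a random intercept. Add it to the regression of iodinated contrast volume as well. If a rank test is used for contrast volume instead, a version stratified by hospital would be the counterpart. State in the same sentences which variable the word stratification refers to. Make the change before any unblinded results are seen.

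The cost is five degrees of freedom as a fixed effect (residual 149 instead of 154 with 156 participants and treatment as the only other term). Hospital is known for every participant, so no new data are needed.

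Adding hospital to the minimisation is optional. It would balance arms within hospital, but in an open-label trial it makes the next allocation easier for local staff to predict, and it would mean changing the allocation algorithm if recruitment has begun. The model term gives most of the benefit without that trade-off.

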### Data collection, management and analysis

#### Data collection methods

Clinical and patient-reported data will be collected by trained research staff at each participating NHS site, supported by the coordinating Clinical Trials Unit (CTU). Data will be collected at baseline, during the index procedure and at follow-up visits at Days 2, 30 and 90, which coincide with routine NHS care.

Baseline data will include demographics, medical history, comorbidities, height, weight and baseline SCr. Procedural data will include details of the intervention, type and volume of contrast used, pain scores using a VAS and any immediate complications.

Follow-up data will include repeat SCr measurements, assessment of adverse events (AEs), MAKE, reinterventions, hospital stay duration and patient-reported outcome measures (EQ-5D-5L and SF-36) at Day 90. Healthcare resource use will be captured via case report forms (CRFs) and participant questionnaires to inform the health economic evaluation.

Optional qualitative data will be collected via semistructured interviews with a purposive sample of participants and practitioners to explore acceptability, feasibility and implementation factors. Interviews will be conducted by trained qualitative researchers following a topic guide.

All data will be entered into a secure, validated electronic data capture system managed by the CTU. Source data verification and monitoring will be conducted according to the trial monitoring plan and Sponsor standard operating procedures (SOPs).

#### Data management and monitoring

Data will be collected via appropriate approved electronic CRFs and software (secure and encrypted) and managed by Leicester Clinical Trials Unit (LCTU).An independent Data Monitoring Committee (DMC) will oversee the trial.Serious AEs will be reported per NHS-established Good Clinical Practice guidelines.Monitoring as per Sponsor SOPs.

#### Trial management

The KID trial will be managed by the LCTU, a UK Clinical Research Collaboration-registered CTU (registration number 43), colocated with the chief investigator (CI) at the University of Leicester (UoL). The LCTU will provide trial management, statistical data and quality oversight support throughout the trial duration. The study is sponsored by the UoL.

Trial oversight will be provided through three key governance structures: the Trial Management Group (TMG), the Trial Steering Committee (TSC) and the DMC. The TMG will meet weekly or as needed and will be responsible for the day-to-day operational management of the trial. It will include the CI, coapplicants, the trial manager, the lead statistician and two lay coapplicants. The lay coapplicants will also liaise with an independent lay advisory group to ensure patient-centred conduct and delivery of the trial. The TSC will meet at least every 6 months. It will be chaired by an independent member and include external clinical, statistical and lay representatives. The TSC will provide high-level oversight, ensure adherence to the protocol and advise on trial progress and conduct.

The DMC will meet separately, prior to each TSC meeting. Comprising independent clinical and statistical experts, including an independent Chair, the DMC will review accumulating trial data with respect to participant safety and data integrity. It will make recommendations to the TSC regarding the continuation, modification or termination of the trial based on these reviews.

